### Assignment of Intervention

#### Allocation

Stratified randomization was used with the strata defined by geographical areas (ie, metropolitan and regional). Within each area, simple randomization (ie, randomization based on a single sequence of random assignments [34]) was performed and participants were assigned to either the provider’s usual care or their services designed and delivered through the SSH technology platform (smart home group). Randomization of participants was undertaken using a computer program and carried out by an independent researcher using anonymized identifiers. The random allocation sequence was delivered through the REDCap application. Allocation occurred after the baseline survey had been completed.

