**Methods:**

This study was designed as a single-blinded, stratified, 12-month randomized controlled trial with participants recruited from three aged care providers in Queensland, Australia. The study aimed to recruit 200 people, including 145 people from metropolitan areas and 55 from regional areas. Participants were randomized to the intervention group (having the SSH platform installed in their homes to assist age care service providers in monitoring and providing timely support) and the control group (receiving their usual aged care services from providers). Data on community care, health and social-related quality of life, health service utilization, caregiver burden, and user experience of both groups were collected at the start, middle (6 months), and end of the trial (12 months).

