**Results:**

The trial recruited its first participant in April 2019 and data collection of the last participant was completed in November 2020. The trial eventually recruited 195 participants, with 98 participants allocated to the intervention group and 97 participants allocated to the control group. The study also received participants’ health service data from government data resources in June 2021.

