## Methods

### Trial Design

The trial was designed as a single-blind, stratified RTC. Participants were divided into two groups with an allocation ratio of 1:1. Trial participants could not be blinded as the intervention required physical installation of equipment in their homes. Researchers undertaking data analyses are blinded to which participants received the intervention. Access to community health services has previously been identified to vary by geographic location [24]. To ensure balance between the intervention and control groups relative to this potential confounder, stratification based on region (ie, metropolitan or regional area) is used.

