### Sample Size

The primary outcome of this trial, the impact of community care for older people, will be evaluated using the ACCOM tool [27], a set of measures of community care suitable for use in the Australian context. The ACCOM mainly uses questions from the Adult Social Care Outcome Toolkit (ASCOT) [33], which is a validated measure of social care related to quality of life. Power was based on a randomized trial design with a clinically important difference of 10% on the primary outcome of ASCOT with a mean 0.80 (SD 0.16) distribution (ie, 0.08, based on previous research [33]). With the threshold of rejecting the null hypothesis of *α*≥.05, effect size of 0.5 (0.08/0.16), and the same allocation ratio of the two groups in our trial. Figure 3 illustrates the relations between total sample size and statistical power.

To achieve 80% statistical power, we needed a total of 134 participants. Allowing for a 30% attrition rate, the sample size of this trial was computed to be 200 participants. We did not anticipate an attrition rate greater than 30% as all participants were existing clients of the participating aged care service providers and received regular visits throughout the trial period. The intervention and outcome measurement collection processes were designed to minimize participant burden. In addition, the power analysis did not consider the repeated-measures design of the trial. Repeated measures increase the power of the trial to find a significant result and appropriate statistical techniques will be applied to ensure that all data available are used in the analyses.

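### Simple randomisation within each region, as described, does not secure the balance on region that stratification is said to ensure

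*Protocol article*

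**What the plan says.** Trial Design explains that access to community health services differs by geography and gives the reason for stratifying: "To ensure balance between the intervention and control groups relative to this potential confounder, stratification based on region". The same section fixes the ratio: "Participants were divided into two groups with an allocation ratio of 1:1".

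Allocation then describes the method. It begins "Stratified randomization was used with the strata defined by geographical areas (ie, metropolitan and regional" and continues "Within each area, simple randomization (ie, randomization based on a single sequence of random assignments". No block, minimisation or other restriction is named. The sequence was computer-generated and delivered through REDCap.

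The abstract gives the planned strata: "The study aimed to recruit 200 people, including 145 people from metropolitan areas and 55 from regional areas". It reports the achieved allocation only overall: "with 98 participants allocated to the intervention group and 97 participants allocated to the control group". The later Results section gives 97, not 98, for the intervention group. Arm counts by region appear nowhere.

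Survey Data Analyses compares the arms at each time point with chi-squared and Wilcoxon rank-sum tests, and fits a log-binomial model only if a difference is significant. Region is not mentioned there. The cost-effectiveness section says that costs will be adjusted for baseline differences, without naming which ones.

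**The concern.** Stratification balances a factor only when allocation inside each stratum is restricted, so that the arms cannot drift far apart there. Simple randomisation imposes no restriction. Splitting one sequence of coin tosses into a metropolitan and a regional sequence leaves every toss independent with probability one half, so nothing is gained. The purpose in Trial Design and the method in Allocation therefore do not fit together.

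Region is the one confounder that the design singles out, so readers will credit the trial with a protection that the described method does not give. What is at stake is unprotected chance imbalance on region, some lost precision where region predicts outcome, and an unsupported statement in the methods. For the primary outcome the stated tests do not make up for this, because a plain rank-sum or chi-squared test ignores region.

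**Working it through.** The article gives no figure for balance to reproduce. Its evaluable sample size of 134 does reproduce, and it does not depend on this point. With an effect size of 0.5, 80% power and alpha 0.05 (taken as two-sided), a rank-sum test with relative efficiency 3/pi needs 67 per arm, or 134 in total.

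**Inputs.** 145 metropolitan and 55 regional (abstract; Table 1 sums to the same: 100 + 25 + 20 and 40 + 15 + 0); 1:1 ratio (Trial Design); simple randomisation in each area (Allocation).

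**Step 1: arm-size difference in each region.** With n independent 1:1 assignments, the intervention count is Binomial(n, 0.5). The difference between arms has SD = sqrt(n).
- Metropolitan: sqrt(145) = 12.0. The 95% range for the intervention count is 61 to 84 of 145.
- Regional: sqrt(55) = 7.4. The 95% range is 20 to 35 of 55.
- A regional split of 33:22 or worse: 2 × P(Binomial(55, 0.5) ≤ 22) = 17.7%.

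None of these results depends on whether the assignments came from one list or two.

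**Step 2: between-arm gap in regional share.** The overall regional share is 55/200 = 0.275. Taking arms of about 100 each, SD ≈ sqrt(0.275 × 0.725 × (1/100 + 1/100)) = sqrt(0.0039875) = 0.063. Simulation lets arm sizes vary (400,000 allocations per row; 100,000 for blocks):

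| Scheme | SD of gap (points) | Chance of a gap over 10 points |
|---|---|---|
| Simple within region (as described) | 6.4 | 11.7% |
| Simple, no strata | 6.3 | 11.6% |
| No strata, arms forced to 100:100 | 6.3 | 11.3% |
| Blocks of 4 within region (illustrative benchmark) | 0.8 | 0% |

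The first two rows are the same distribution, and the small differences are simulation noise. The last row shows what stratification would have delivered with a restriction inside each region. The block size is an assumption made only for that comparison.

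**Step 3: does the overall split show regional balance?** Under simple randomisation of 195, a 98/97 split in either direction has probability 2 × P(Binomial(195, 0.5) = 97) = 11.4%. It therefore fits simple randomisation and would equally fit an undescribed restricted list. The third row above shows that even exactly equal arms leave the regional-share gap about as variable as before.

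**Step 4: possible effect on the primary outcome.** A gap g in regional share shifts the arm difference by g × (regional mean minus metropolitan mean). The article does not give that difference between regions, so a range is assumed. The scale comes from the Sample Size section: "clinically important difference of 10% on the primary outcome of ASCOT with a mean 0.80 (SD 0.16) distribution", a target difference of 0.08.
- Difference between regions 0.08, gap 10 points: 0.10 × 0.08 = 0.008, which is 0.05 SD or one tenth of the target.
- Difference between regions 0.16 (one full SD), gap 10 points: 0.10 × 0.16 = 0.016, which is 0.10 SD or one fifth of the target.

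**The case against.** Several points on the other side have force.

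- **Simple randomisation is valid.** It does not bias the comparison in expectation, and the nominal error rate of the tests already allows for chance imbalance. This stands. On the assumptions in step 4, the likely distortion of the primary outcome is also modest.
- **The wording may be loose.** The list may have been blocked and only described badly. This is possible, but the article both names and defines the method, so as it stands the text contradicts its purpose. Checking the list settles it.
- **Covariates may be listed in an analysis plan that is not shown.** This stands for the regression models, whose covariates the article does not list. It does not cover the first-line survey tests, which are named and carry no stratum.

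A reader might also infer stronger conclusions that the document does not support:

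- **That balance on region failed.** No region-by-arm counts are reported, and the balance obtained could be good. One can say only that the described method does not secure it.
- **That nothing in the plan handles region, so imbalance passes straight into costs.** The cost-effectiveness section states adjustment for baseline differences. It does not name region, but it cannot be read as ruling region out.
- **That provider should be handled in the same way.** Provider was not a stratification factor, so the argument here does not extend to it.

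**Conclusion.** The point holds as a mismatch between stated method and stated purpose. Simple randomisation within region gives the same chance imbalance on region as no stratification: an SD of about 6.4 points in the regional-share gap, about a 12% chance of a gap of 10 points or more, and a 17.7% chance of 33:22 or worse among the regional participants. These figures rest on the planned 145/55 strata and on the Allocation text being literally true. The trial is not invalidated and the sample size is unaffected. The protection claimed in Trial Design is absent, however, and the survey comparisons, including ACCOM, are stated without region. This should be corrected while the final analysis, described in the Results section as underway, is still open.

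**What to change.** 1. Check the allocation list. If blocks or another restriction were used within region, correct the Allocation section to say so. If not, withdraw the statement in Trial Design that stratification ensures balance.
2. In either case, report the counts by region and arm, and reconcile the 98 and 97 given for the intervention group.
3. Account for region in the between-arm survey analyses: for example, a region-stratified rank-sum (van Elteren) test in place of the plain rank-sum test, and region as a covariate in the regression models.
4. Name region among the baseline differences for which costs will be adjusted.

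The cost is some wording and a small change of test for the survey outcomes, using a variable already recorded. Because the data are in, settle the change while the analysts are still blinded, and show the unstratified results alongside. Allocation is complete, so nothing in the randomisation itself can now be changed.

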#### SSH Kit Installation

Once participants had been consented, a set of surveys was administered by the project officer. The participants allocated to the intervention group received an SSH kit. Installation of the SSH kit (tablet, hub, sensors) was coordinated by the project officer, typically within 2 weeks of consent and randomization. A user sheet that describes how to interact with the tablet and interpret the information presented on the tablet SSH app was included with the kit. The project officer also demonstrated to the participant how to use the tablet and the SSH app during installation. To obtain valid baseline data after installation, the SSH system gathered 14 days of the participants’ normal living routines in their homes. After the baseline data had been gathered, the identified aged care service providers and the nominated family portal users were notified of their user ID, password, and access instructions. During the trial period, the project officer was the point of contact for any problems or questions. Technical issues that were not easily addressable were escalated to the research technical team who worked to find efficient and effective solutions. All reported issues, no matter how minor, were reported to the project manager for inclusion in the monthly project reports. If a participant wished to withdraw from the trial, the project officer arranged for an uninstall to occur as quickly as possible from the home. Upon completion of the project, all homes had their trial equipment removed by the project officer. Participants allocated to the usual care group continued to receive their existing care and social services in line with local aged care service provider protocols for the 12 months of the trial. They did not have any SSH equipment installed in their homes.

### Measurements and Data Collection

#### Overview

Data were collected from participants, informal carers, and aged care service providers from state and national government data sources and home-based sensor systems. These included surveys, raw sensor data, and interview information. The state and national government data sources included hospital linkage data and MBS/PBS data. The measure, context, score meaning, and time points of collection are presented below.

#### Survey Questionnaires

##### Baseline

The project officers administered a baseline survey to all consented participants. Questionnaires included in the baseline survey are listed in Table 2. Note that the Abbreviated Mental Test Score (AMTS) was administered by a project officer prior to administering the baseline survey. Follow-up questionnaires at the mid-trial point (around 6 months) and end-trial point (around 12 months) included the same battery of questionnaires except for the demographics and AMTS. The baseline survey was delivered to participants during the consent face-to-face meeting and took approximately 45 minutes to complete.

**Table 2 table2:** Survey questionnaires.

Domain	Measure	Context	Score meaning/presentation	Time point		
				Start	Mid	End
Demographic information	Individual questions	Gender, age, weight and height (BMI), occupation, marital status, income, computer skills, social media, and NBN^a^ connectivity	Individual and coded scores	✓		
Cognitive level	Abbreviated Mental Test Score (AMTS) [35]	To establish baseline cognition (10 questions)	Maximum score 10; a score of less than 7 or 8 suggests cognitive impairment	✓		
Impact of care: participant	ACCOM^b^ measure (adapted from ASCOT^c^ for the Australian population) [33]	Self-completion (eight attributes): control over daily life, personal cleanliness and comfort, food and drink, personal safety, social participation and involvement, occupation, accommodation cleanliness and comfort, dignity. Additional questions: subjective rating of health, open question	Four levels: Ideal State, No needs, Some needs, High needs; ASCOT scoring [36]	✓	✓	✓
Health-related quality of life	EQ5D^d^ [37]	Five generic questions on health status: mobility, self-care, usual activities, pain/discomfort, anxiety/depression; respondents’ self-rated health is recorded on a vertical, visual analog scale (VAS: 0-100)	Results presented as an index value (Australian Scoring algorithm); VAS presented as a number from 0 to 100, with 0 indicating the worst and 100 indicating the best imaginable health state	✓	✓	✓
Activities of Daily Living (ADL)	Katz’s ADL [29]	Assesses basic ADLs: feeding, continence, transferring, toileting, dressing, bathing	Maximum score of 6 points indicating fully independent, 4 points indicating moderately impaired, and 2 points indicating severely impaired	✓	✓	✓
Instrumental Activities of Daily Living (iADL)	Lawton’s iADL [30]	Assesses a person’s ability to perform daily tasks, measuring eight domains: using the telephone, shopping, preparing food, housekeeping, doing laundry, using transportation, handling medications, handling finances	Summary score from 0 (low function) to 8 (high function)	✓	✓	✓
Depression	Geriatric Depression Scale (Short Form) [31]	15-item version, used to identify depression in older people	Scores >5 (yes) suggest presence of depression; scores >10 are almost always depression	✓	✓	✓

^a^NBN: National Broadband Network.

^b^ACCOM: Australian Community Care Outcome Measurement.

^c^ASCOT: Adult Social Care Outcome Toolkit.

^d^EQ5D: 5-dimension EuroQuol.

##### Follow-Up

Participants were contacted by a project officer to complete the same surveys at mid-trial and end-trial. These were preferably conducted over the phone, and particularly during imposed COVID-19 safety measures. For the intervention group, an uninstall of the SSH kit typically took place at the same time as the end-trial survey was administered. Follow-up was systematized through the REDCap system. For participants who withdrew from the trial, all data collected up to the point of withdrawal are included in the analysis of the study, unless formally requested not to be by the participant. This was outlined in the Participant Information and Consent Form (Multimedia Appendix 1) and participants were asked to consent to the inclusion of their data.

#### Sensor Data

All in-home raw sensor data were transferred to the IoT router and then collected directly to a secured server where all sensor and participant data were gathered. Storage of and access to the project data within the data center were governed by privacy policy and procedures, and limited to the investigators on this project. Data center operations staff had access to the data to perform their normal duties (eg, database backup).

The data gathered through the in-home sensors were categorized into daily living activity domains, as listed in Table 3.

The data were not live-monitored in the trial. Participants were made aware of this prior to the trial commencing to ensure that a false sense of security was not assumed.

Figure 4 shows the spread of sensors installed in the household of the smart home group participants and Figure 5 provides a description of the SSH sensors deployed and where they were installed in the home.

**Table 3 table3:** The mapping of sensors to daily living activity domains.

Daily living activities	Sensor type	Location
Indoor walking	Motion sensor	All rooms
Sit-stand transition times (out of a bed/chair)	Accelerometer, pressure sensor, sleep sensor	Bedroom, living room
Meal preparation	Motion sensor, electrical power sensor, accelerometers	Dining room, kitchen
Hygiene	Motion sensor, humidity sensor, temperature sensor	Bathroom
Dressing	Motion sensor, accelerometer	Wardrobe

**Figure 4 figure4:**
[figure not shown]
Passive sensors installed in the household to support independent living.

**Figure 5 figure5:**
[figure not shown]
Description of Smart Safer Homes sensors deployed, the data gathered, and where these sensors were installed.

#### Informal Carer(s)

Data on the burden experienced by the informal carers of the people participating in the trial were collected using the 4-item Zarit Screen (ZBI-12) survey [32] at all three time points (start, mid-trial, and end-trial). The ZBI-12 is a valid and reliable instrument for measuring the burden of carers. A total ZBI-12 score ranges from 0 to 48 based on the summation of 12 items; a score of 0-10 indicates no to a mild burden, 10-20 indicates a mild to moderate burden, and >20 indicates a high burden. The individual(s) identified as informal carer(s) by the participant were contacted by phone or email and the questionnaire was posted out or delivered through email (depending on preference).

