#### Secondary Outcomes

The secondary outcomes included change in health-related quality of Life, as measured by the Five-Dimension EuroQuol (EQ5D 5-L) questionnaire [28]; Katz ADL [29] and instrumental ADL (Lawton iADL [30]); depression (Geriatric Depression Scale [31]); health service utilization, including community prescription medicines (collected based on Pharmaceutical Benefit Scheme [PBS] claims data), community health services (including nonreferred medical attendances such as general practitioner appointments, attendances with medical specialists, pathology, diagnostic imaging, and Allied Health attendances collected from Medical Benefit Scheme [MBS] claims data), hospital attendances (same day and overnight admitted), and emergency department presentations (collected from QLD public hospital data); changes in service design, adoption, and aged care service provider experiences (based on provider staff interviews); care giver burden (Zarit Burden Interview [ZBI]-12 [32]); and costs to deliver the SSH supported care.

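### The carer-burden instrument is described inconsistently: a 4-item screen in name, a 12-item ZBI-12 in scoring, with two burden bands that share the score of 10

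*Protocol article*

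**What the plan says.** Under Secondary Outcomes, the protocol article lists "care giver burden (Zarit Burden Interview [ZBI]-12 [32", that is, the 12-item version with its reference. Under Informal Carer(s), it says that the data were "collected using the 4-item Zarit Screen (ZBI-12) survey" and were taken "at all three time points (start, mid-trial, and end-trial". The same paragraph then gives the scoring: "A total ZBI-12 score ranges from 0 to 48 based on the summation of 12 items". Three bands follow. For the lowest, "a score of 0-10 indicates no to a mild burden"; for the other two, "10-20 indicates a mild to moderate burden, and >20 indicates a high burden".

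Table 2 does not include the carer instrument, and the abbreviation list expands ZBI without an item count. The Survey Data Analyses section plans chi-square and Wilcoxon rank-sum tests between groups at each time point, a log-binomial model where a difference is significant, and Friedman and signed-rank tests within groups. It plans these for survey results in general and does not say which form of the carer-burden score, total or banded, enters which test.

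**The concern.** The sentence that identifies the fielded questionnaire gives it two incompatible descriptions, and the scoring text fits only one of them. A reader cannot be certain which form the carers filled in, or therefore which range and bands apply to the data.

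The bands are also not mutually exclusive, so one score has two possible classes. If the classes are used, someone must decide where that score goes, and the decision is better made before the results are seen.

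Carer burden is the seventh aim, a listed secondary outcome and part of the expected findings. The Results section says that the final analysis is still in progress, so a clarification is still useful. The primary outcome and the sample size do not depend on it.

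**Working it through.** **Inputs, all from Informal Carer(s).** Label: 4-item screen, also called ZBI-12. Number of items summed: 12. Range of the total: 0 to 48. Bands: 0-10, 10-20 and above 20. The points per item are not stated.

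**Step 1: reproduce the stated range.** Implied maximum per item = 48 / 12 = 4. Then 12 × 4 = 48, so the 0 to 48 range is coherent for a 12-item form with items scored 0 to 4. There is no miscalculation; the fault is an inconsistency of description.

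**Step 2: the 4-item label.** A form with 4 items cannot produce a sum of 12 items. This holds whatever the item scale.

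**Step 3: what the stated scoring would mean for a 4-item form.** This step needs an assumption about item scoring.
- With the inferred 0 to 4 scale, the maximum is 4 × 4 = 16. This is below 48 and below the threshold of 20, so the top band would be out of reach.
- On other scales, four items would reach 48 only with a maximum of 48 / 4 = 12 points per item. They would exceed 20 only with a maximum above 20 / 4 = 5 points per item. The article mentions neither scale.

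**Step 4: check the bands over every whole-number total from 0 to 48.**

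| Total | Number of values | Band |
|---|---|---|
| 0 to 9 | 10 | lowest only |
| 10 | 1 | lowest and middle |
| 11 to 20 | 10 | middle only |
| 21 to 48 | 28 | top only |

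The values add up: 10 + 1 + 10 + 28 = 49. Exactly one total is assigned twice, and none is left out.

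**Step 5: which planned analyses depend on this.** The rank-sum, Friedman and signed-rank tests can be run on the total, and the total does not use the bands. They are unaffected as long as one form was used throughout. The log-binomial model needs a binary outcome, and a chi-square test needs categories. The bands are the only categories that the article gives for this instrument, so these two analyses would depend on the band definitions if they are applied to carer burden.

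**The case against.** The strongest reply is that the text is one-sided. The outcome list says ZBI-12, the carer paragraph repeats that name, and the item count and range given there agree with each other. Against this stands a single descriptor. That is a good reason to think it a slip, and this point stands. It does not close the matter, because the descriptor sits in the sentence that reports what was collected and no other text corrects it.

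The second reply is that the overlap is loose boundary notation that touches one score of 49 and matters only if categories are reported. This also stands. It limits the size of the problem but does not say where the score of 10 belongs.

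A reader might infer two stronger conclusions that the document does not support.
- **That no carer could be classed as high burden.** This requires that a 4-item form was really used, that its items score 0 to 4, and that its totals were read against the 12-item bands. The article establishes none of the three.
- **That a banded chi-square comparison would be invalid.** The article does not say that the totals will be banded. Even in that hypothetical case, a top band that is empty in both arms leaves a two-category table. The categories would be mislabelled, but the between-group test would not be invalid for that reason.

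**Conclusion.** The point holds as an internal inconsistency in the definition of a secondary outcome, not as an arithmetic error. Two things are wrong as written: the instrument is called a 4-item screen but scored as a 12-item one, and the two lower bands overlap.

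The size is modest. On the 12-item reading, which the text favours, only the score of 10 is ambiguous, and only in categorised results. On the 4-item reading, the printed range and bands would not apply at all; the maximum of 16 for that case rests on the inferred item scale. The conclusion that the total score is unaffected assumes that one form was used for all carers at all three time points.

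**What to change.** 1. Check the questionnaire actually given to carers. State one version, with its item count and score range, and remove the other description.
2. Before any categorised analysis, rewrite the bands so that each total falls in exactly one. The article does not show which band takes 10, so this must come from the scoring source that it cites for the instrument.
3. As a separate improvement that the inconsistency does not itself require, make the total score, adjusted for the carer's baseline score, the main between-group comparison for this outcome. The baseline score has already been collected, and the general plan otherwise compares the groups at each time point without using it.

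The first two changes cost one form check, one look at the cited source and a corrected sentence or two. The third needs no new data, only a line in the analysis plan.
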